## Abstract

**Background:**

Gait disorders and cognitive impairments are prime causes of disability and institutionalization after stroke. We hypothesized that relative to single-task gait rehabilitation (ST GR), cognitive-motor dual-task (DT) GR initiated at the subacute stage would be associated with greater improvements in ST and DT gait, balance, and cognitive performance, personal autonomy, disability, and quality of life in the short, medium and long terms after stroke.

**Methods:**

This multicenter (*n*=12), two-arm, parallel-group, randomized (1:1), controlled clinical study is a superiority trial. With *p*<0.05, a power of 80%, and an expected loss to follow-up rate of 10%, the inclusion of 300 patients will be required to evidence a 0.1-m.s^−1^ gain in gait speed. Trial will include adult patients (18–90 years) in the subacute phase (0 to 6 months after a hemispheric stroke) and who are able to walk for 10 m (with or without a technical aid). Registered physiotherapists will deliver a standardized GR program (30 min three times a week, for 4 weeks). The GR program will comprise various DTs (phasic, executive function, praxis, memory, and spatial cognition tasks during gait) in the DT (experimental) group and gait exercises only in the ST (control) group. The primary outcome measure is gait speed 6 months after inclusion. The secondary outcomes are post-stroke impairments (National Institutes of Health Stroke Scale and the motor part of the Fugl-Meyer Assessment of the lower extremity), gait speed (10-m walking test), mobility and dynamic balance (timed up-and-go test), ST and DT cognitive function (the French adaptation of the harmonization standards neuropsychological battery, and eight cognitive-motor DTs), personal autonomy (functional independence measure), restrictions in participation (structured interview and the modified Rankin score), and health-related quality of life (on a visual analog scale). These variables will be assessed immediately after the end of the protocol (probing the short-term effect), 1 month thereafter (the medium-term effect), and 5 months thereafter (the long-term effect).

**Discussion:**

The main study limitation is the open design. The trial will focus on a new GR program applicable at various stages after stroke and during neurological disease.

**Trial registration:**

NCT03009773. Registered on January 4, 2017.

**Supplementary Information:**

The online version contains supplementary material available at 10.1186/s13063-023-07138-x.

## Administrative information

Note: the numbers in curly brackets in this protocol refer to SPIRIT checklist item numbers. The order of the items has been modified to group similar items (see http://www.equator-network.org/reporting-guidelines/spirit-2013-statement-defining-standard-protocol-items-for-clinical-trials/).

## Introduction

### Background and rationale {6a}

Stroke is the main cause of acquired, severe disability [1, 2]. The overall burden of stroke (quantified as disability-adjusted life years) is increasing worldwide [3]. Post-stroke sensorimotor and perceptual impairments can limit gait and thus restrict community ambulation. Indeed, gait and balance complaints are expressed by 80% of survivors 3 months after the stroke [1, 4, 5]. Gait disorders constitute a key marker of recovery from stroke [6] and are significantly and independently associated with disability [7], institutionalization, and death [8–10]. This is why stroke neurorehabilitation focuses on gait and thus improvements in the patients’ survival, personal autonomy, social inclusion, and quality of life (QoL) [8, 11–13].

Although gait rehabilitation (GR) is effective for motor impairments [14–16], falls remain a major risk factor for stroke complications [16, 17]. The development of effective methods for balance and mobility rehabilitation is a priority for stroke patients, their caregivers, and healthcare professionals [18]. Although GR is often effective for gait during rehabilitation sessions, the transfer of gait skills to daily living is more challenging; this discrepancy can be due to a change in attention, which is focused on gait during the training session but not on gait in everyday life [19–21]. These observations suggest that cognitive-motor interference (CMI) is a major contributor to activities of daily living after stroke [19–21].

It is known that CMI is abnormally frequent among stroke victims [20]. Dual-task (DT) walking can be used to evaluate CMI and attention-demanding mobility functions after stroke [22, 23]. Community ambulation, social inclusion, and QoL require the ability to simultaneously walk and execute one or more cognitive tasks [9, 24–27]. Poor functional mobility after stroke appears to be linked to worsened DT ability and attentional impairments [28]. CMI can account for the greater relative deterioration in DT performance than in single task (ST) performance [29]. This DT deterioration has been attributed to the greater attentional allocation needed to compensate for the gait impairment (requiring functional executive networks) [22]. Executive functions are often impaired after a stroke, and these higher cognitive processes (e.g., volition, planning, purposive action, action monitoring, and cognitive inhibition) are required for the coordination of cortical sensory-motor systems during DT [30]. Several theoretical frameworks for CMI have been put forward [21]. Firstly, the central capacity-sharing model holds that the two tasks have to share the available processing resources; hence, performance worsens when the demand overloads the limited attentional-sharing capacity [31, 32]. Secondly, the bottleneck model holds that each task may need simultaneous access to a processor that can only act with one input at a time; hence, the processing of the second task has to be postponed [21, 33, 34]. Thirdly, the cross-talk model predicts that tasks from different networks disturb each other (through cross-talk) but that tasks from the same network do not [35].

The new SYNCOMOT (“SYNergie Cognitivo-MOTrice” in French, which means “cognitive motor synergy” in English) GR protocol addresses the CMI problem by seeking to leverage cognitive-motor synergy in the executive function network [21, 36, 37]. Whereas automatic walking and rhythmic ST walking stimulate subcortical locomotor regions of the brain, DT walking involves a direct locomotion pathway (i.e., the primary motor cortex, cerebellum, and spinal cord) and an indirect locomotion pathway (i.e., the prefrontal cortex, premotor areas, supplementary motor area, and basal ganglia) [21, 38]. Motor and cognitive therapies are essential components of stroke rehabilitation but are generally performed separately and not simultaneously [16, 24]. Rehabilitation programs based on CMI have shown moderate efficacy in the chronic post-stroke phase [39–42] and in degenerative diseases [42–44]. Randomized controlled trials have assessed the motor and cognitive effects of DT or multitask GR protocols in the chronic post-stroke phase and in other neurological diseases but not at the sub-acute post-stroke stage [28, 39, 44–46]. To the best of our knowledge, this is the first randomized, controlled study of DT GR at the sub-acute stage of stroke. The DT GR program is focused on interactions between motor activity on one hand and five cognitive activities (executive functions, spatial exploration, phasic functions, memory functions, and prehension) on the other.

### Objectives {7}

The primary objective of the trial described here is to determine whether long-term gait velocity is greater after DT GR than after ST GR. The secondary objectives are to compare DT GR and ST GR with regard to motor performance (lower limb motricity, gait, and balance), cognitive performance, personal autonomy, disability, and QoL in the short, medium, and long term after stroke, as a function of the stroke victim's gait characteristics and plasticity after stroke.

### Trial design {8}

SYNCOMOT is a multicenter (*n*=12), prospective, two-arm, parallel-group, randomized [1:1], stratified, controlled superiority trial conducted in France.

## Methods: participants, interventions, and outcomes

### Study setting {9}

Patients will be recruited by neurorehabilitation departments at 12 clinics, general hospitals, and university medical centers in northern France: Amiens Picardie University Medical Center (the coordinating center, in Amiens), Arras General Hospital (Arras), Beauvais General Hospital (Beauvais), the Centre Jacques Calvé clinic (Berck-sur-Mer), the Institut Medical de Breteuil clinic (Breteuil), Caen University Medical Center (Caen), Compiegne General Hospital (Compiegne), the Centre de Réeducation des Trois Vallées clinic (Corbie), Lille University Medical Center (Lille), the Centre L'Espoir clinic (Lille), the Centre Le Belloy clinic (Saint Omer-en-Chaussée), and Rouen University Medical Center (Rouen). The study flow chart for screening, enrolment (after the provision of written, informed consent), and randomization is shown in Fig. 1.

**Fig. 1 Fig1:**
[figure not shown]
Study design and flow diagram. MRI, magnetic resonance imagery; fMRI, functional MRI; fMRS, functional magnetic resonance spectroscopy

### Eligibility criteria {10}

The inclusion criteria will be as follows: (i) age between 18 and 90, (ii) admission to a rehabilitation department within 6 months of a first ischemic or hemorrhagic stroke with positive brain imaging findings (computed tomography (CT) or magnetic resonance imaging (MRI) of the brain), (iii) ability to provide informed consent, (iv) ability to walk at least 10 m (with or without a technical aid) at a speed below 1.2 m.s^−1^, and (v) social security coverage. The exclusion criteria will be (i) prestroke locomotor or neurological disorders affecting gait, (ii) visual or hearing disorders that impair communication, (iii) severe aphasia, (iv) participation in another interventional study of gait or cognitive rehabilitation, (v) pregnancy or breastfeeding, and (vi) administrative supervision (legal guardianship or incarceration).

### Who will take informed consent? {26a}

All participants will be fully informed about the trial’s objectives and procedures by rehabilitation specialists (Physical Medicine and Rehabilitation (PM&R) physicians) and will give their written, informed consent to the center’s lead investigator (also a rehabilitation specialist) prior to inclusion. Participants will be informed in the patient information leaflet that the study data will be kept safe.

### Additional consent provisions for collection and use of participant data and biological specimens {26b}

Not applicable.

## Interventions

### Explanation for the choice of comparators {6b}

The DT GR program is focused on interactions between motor activity on one hand and five cognitive activities (executive functions, spatial exploration, phasic functions, memory functions, and prehension) on the other. The trial will compare the short-, medium- and long-term effects of a DT protocol vs. a ST protocol initiated during the sub-acute post-stroke period.

### Intervention description {11a}

GR program is based on a personalized, progressive DT approach; with repetitive, goal-oriented tasks. At each site, at least two trained physiotherapists will deliver the intervention in the two parallel groups. The GR sessions will include 30 min of physical therapy on 3 days a week for 4 weeks after inclusion (i.e., 12 sessions in total), instead of the patient’s standard rehabilitation sessions on those days. Each 30-min session will consist of five different 5-min exercises, with 1 min of rest between each exercise. The GR protocols will focus on ST gait or on cognitive-motor DT gait. The patient’s progression through the protocol will be standardized according to the self-assessed cognitive and motor burdens (rated on visual analog scales (VASs)) at the end of each session. If the cognitive or motor burden of the last session is below 7 on the VAS, the intensity in the next session will be incremented by one level. Ideally, the intensity of the patient’s GR will increase week after week. If the patient fails an exercise or session, it will be replaced by the last exercise or session in which the patient was successful. The sessions’ functional task training will combine intensity with functional relevance [16]. The care providers’ adherence to the rehabilitation protocol will be evaluated during study monitoring visits.

#### The control group: ST GR program (Table 1)

The ST GR program will be composed of 5-min gait exercises in five different walking directions: forwards, sideways on the healthy side, sideways on the hemiparetic side, backwards, and stepping up over obstacles or foam mats). As mentioned above, progression over the 4 weeks will depend on the self-assessed motor burden (VAS score) at the end of each session. The intensity of the ST gait protocol will be increased by adding weight on the hemiparetic side, increasing the gait speed, increasing the height of the obstacles, and increasing balance constraints (having to walk along a line). Depending on the patient's progression through the gait protocol, up to 12 intensity levels can be performed. If a patient fails an exercise or session, she/he will repeat the last successfully completed exercise or session (so as not to waste the 30 min of GR).

**Table 1 Tab1:** The standardized ST GR protocol

Progression	Five types of 5-min gait exercises (30 min per session, 3 times a week on D1, D2, and D3)	Level of motor difficulty
**Week 1**	- Walking forwards - Walking sideways on the healthy side - Walking sideways on the hemiparetic side - Walking backwards - Walking and crossing flat obstacles	1/ Comfortable walking 2/ Walking with weights (100–250 g) 3/ Walking along a line
	If an exercise is impossible, the patient will repeat the last successfully completed exercise or session (so as not to waste the 30 min of GR).	
**Week 2**	- Walking forwards - Walking sideways on the healthy side - Walking sideways on the hemiparetic side - Walking backwards - Walking and crossing obstacles	4/ Comfortable walking with weights (100–250 g) 5/ Comfortable walking with weights (250–500 g) 6/ Comfortable walking and crossing obstacles <5 cm in height
	If an exercise is impossible, the patient will repeat the last successfully completed exercise or session (so as not to waste the 30 min of GR).	
**Week 3**	- Walking forwards - Walking sideways on the healthy side - Walking sideways on the hemiparetic side - Walking backwards - Walking on a foam carpet	7/ Fast walking 8/ Fast walking with weights (100–250 g) 9/ Fast walking on a foam carpet
	If an exercise is impossible, the patient will repeat the last successfully completed exercise or session (so as not to waste the 30 min of GR).	
**Week 4**	- Walking forwards - Walking sideways on the healthy side - Walking sideways on the hemiparetic side - Walking backwards - Walking on a foam carpet	10/ Fast walking with weights (100–250 g) 11/ Fast walking with weights (250–500 g) 12/ Fast walking and crossing obstacles <10 cm in height
	If an exercise is impossible, the patient will repeat the last successfully completed exercise or session (so as not to waste the 30 min of GR).	

#### The experimental group: DT GR program (Table 2)

The DT GR program will be composed of five different 5-min cognitive-motor DTs. The DT gait exercises will be related to instrumental activities of daily living after a stroke and will involve both internal interfering functions (executive functions, phasic functions, memory, and prehension) or external interfering functions (spatial cognition). The therapist will not encourage the patient to prioritize one task over another, i.e., the patient will be free to favor (or not) one of the two tasks if she/he wishes. The difficulty over 4 weeks will be assessed according to the motor and cognitive burdens during the GR program (self-assessed on VASs at the end of each session). The cognitive difficulty will be based on three types of sound environment: quiet, noisy with the patient’s favorite music (chosen on the YouTube website), or the France Info news radio station. If a DT exercise cannot be completed, it will be replaced by another DT exercise, such as a calculation task or a previously completed task (so as not to waste the 30 min of GR).

**Table 2 Tab2:** The standardized DT GR protocol

Progression	Five types of 5-min gait exercise (30 min per session, 3 times a week (on days (D)1, D2, and D3)	Level of motor difficulty	Level of cognitive difficulty
**Week 1**	- Walking during an executive function task: go/no-go letters (D1: letter “A,” D2: letter “B,” D3: letter “Z”) - Walking during a memory task: minus -2 span - Walking while holding an object in the healthy hand: a half-full glass of water - Walking during a semantic fluency task (D1 animals, D2 fruits, D3 supermarket articles) - Walking during while looking for targets in the space ahead (D1 objects, D2 images, D3 words)	1/ Comfortable walking 2/ Walking with weights (100–250 g) 3/ Walking along a line	1/ A quiet environment 2/ Music selected by the patient 3/ News radio (France Info)
	If an exercise is impossible, replace it with a calculation (plus 2) and the following starting numbers: 0, 1, 14, 43, 128 (5 × 1 min). If this is impossible, count backwards or forwards, depending on the patient's abilities.		
**Week 2**	- Walking during an executive function task: go/no-go Letters (D1: letter “A,” D2: letter “B,” D3: letter “Z”) - Walking during a memory task: minus −1 span - Walking while holding an object in the healthy hand: a 75%-full glass of water - Walking during a semantic fluency task (D1 kinds of bird, D2 towns, D3 colors) - Walking during while looking for targets on the healthy side (D1 objects, D2 images, D3 words)	4/ Comfortable walking with weights (100–250 g) 5/ Comfortable walking with weights (250–500 g) 6/ Comfortable walking and crossing obstacles <5 cm in height	1/ A quiet environment 2/ Music selected by the patient 3/ News radio (France Info)
	If an exercise is impossible, replace it with a calculation (plus 3) and the following starting numbers: 0, 1, 14, 43, 128 (5 × 1 min). If this is impossible, count backwards or forwards, depending on the patient's abilities.		
**Week 3**	- Walking during an executive function task: go/no-go numbers - Walking during a memory task: minus −2 alphabetic span - Walking while holding an object in the paretic hand: a half-full glass of water - Walking during an alternating semantic fluency task (D1 animals/fruits, D2 fruits/vegetables, D3 fruits/supermarket articles) - Walking while looking for targets on the paretic side (D1 objects, D2 images, D3 words)	7/ Fast walking 8/ Fast walking with weights (100–250 g) 9/ Fast walking on a foam carpet	1/ A quiet environment 2/ Music selected by the patient 3/ News radio (France Info)
	If an exercise is impossible, replace it with a calculation (minus 2) and the following starting numbers: 0, 1, 14, 43, 128 (5 × 1 min). If this is impossible, count backwards or forwards, depending on the patient's abilities.		
**Week 4**	- Walking during an executive function task: go/no-go numbers - Walking during a memory task: minus −1 alphabetic span - Walking while holding an object in the paretic hand: a 75%-full glass of water - Walking during an alternating semantic fluency task (D1 kinds of fish/bird, D2 fruits/towns, D3 colors/furniture - Walking while looking for targets in the space behind (D1 objects, D2 images, D3 words)	10/ Fast walking with weights (100–250 g) 11/ Fast walking with weights (250–500 g) 12/ Fast walking and crossing obstacles <10 cm in height	1/ Quiet environment 2/ Music selected by patient 3/ News radio (France Info)
	If an exercise is impossible, replace it with a calculation (minus 3) and the following starting numbers: 0, 1, 14, 43, 128 (5 × 1 min). If this is impossible, count backwards or forwards, depending on the patient's abilities.		

### *Criteria for discontinuing or modifying allocated interventions {11b}*

In the standardized ST GR protocol, if an exercise is impossible, the patient will repeat the last successfully completed exercise or session (so as not to waste the 30 min of GR) or will perform a calculation (week 1: addition “plus 2,” week 2: addition “plus 3,” week 3: subtraction “minus 2,” and week 4: subtraction “minus 3,” with the following starting numbers: 0, 1, 14, 43, 128 (5 × 1 min)). If this is impossible, the patient will count backwards or forwards, depending on his/her abilities. If the GR protocol is suspended for medical reasons (an acute health problem), the 30-min sessions will be rescheduled so that all 12 are achieved within 31 days. Allocated interventions will not be modified.

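### Section {11b} gives the control arm the calculation fallback that Table 2 assigns to the dual-task arm, contradicting Table 1

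*Protocol article*

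**What the plan says.** The article states the control-arm fallback in more than one place, and the statements differ.

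- **Section {11b}** opens on the control arm by name: "In the standardized ST GR protocol, if an exercise is impossible, the patient will repeat the last successfully completed exercise or session". It then adds an alternative, "or will perform a calculation (week 1: addition", and continues with one operation per week. It ends with a last resort: "If this is impossible, the patient will count backwards or forwards, depending on his/her abilities".
- **The control-arm description** gives one remedy: "If a patient fails an exercise or session, she/he will repeat the last successfully completed exercise or session".
- **Table 1** gives the same remedy in each of its four weekly rows: "If an exercise is impossible, the patient will repeat the last successfully completed exercise or session". It mentions neither calculation nor counting.
- **The DT-arm description** says of a DT exercise that cannot be completed: "it will be replaced by another DT exercise, such as a calculation task or a previously completed task".
- **Table 2** (DT arm) spells this out by week, from "replace it with a calculation (plus 2) and the following starting numbers" in week 1 to "replace it with a calculation (minus 3) and the following starting numbers" in week 4, with counting if calculation is not possible.

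The Methods part of the abstract restricts the control programme to gait exercise, and section {11d} bars DT training outside the schedule.

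**The concern.** The primary objective is to compare DT with ST gait rehabilitation, and the two programmes are meant to differ in whether a cognitive task is added to gait. Section {11b} permits, in the control arm, the task that serves as the DT arm's own substitute exercise.

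Two things are at stake. First, some control patients may receive part of what is being tested, or lose gait practice to a cognitive task. Second, the control may differ between centres: one that follows {11b} delivers something different from one that follows Table 1. There are 12 centres, and the Discussion says the same care providers deliver both programmes, so every therapist will already know the calculation task.

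The fallback is triggered when an exercise is impossible, so any exposure would fall on the patients who struggle with the set exercises and not on a random subset.

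**Working it through.** **1. The rules side by side**

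| Element | {11b}, ST arm | Table 1, ST arm | Table 2, DT arm |
|---|---|---|---|
| Repeat last completed exercise or session | yes | yes, 4 of 4 weeks | not in the table; the DT-arm text allows a previously completed task |
| Week 1 operation | plus 2 | none | plus 2 |
| Week 2 operation | plus 3 | none | plus 3 |
| Week 3 operation | minus 2 | none | minus 2 |
| Week 4 operation | minus 3 | none | minus 3 |
| Starting numbers | 0, 1, 14, 43, 128 | none | 0, 1, 14, 43, 128 |
| Format | 5 × 1 min | none | 5 × 1 min |
| Last resort | counting | none | counting |

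Section {11b} agrees with Table 2 on 4 of 4 operations, 5 of 5 starting numbers, the format and the last resort. On all of these it departs from Table 1. It gives no separate rule for the DT arm.

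**2. Size of one substitution**

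Inputs from {11a}: five 5-minute exercises per session, and 12 sessions.

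- Exercise time per session: 5 × 5 = 25 min.
- Exercise time in the programme: 12 × 25 = 300 min, or 12 × 5 = 60 slots.
- One calculation fallback: 5 × 1 = 5 min, which is one full slot.
- Share of a session: 5/25 = 20%.
- Share of the programme: 5/300 = 1.7%.

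Total exposure would be this amount times the number of substitutions, which the article does not give.

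**3. Sensitivity of the trial to a loss of contrast (illustration only)**

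The concern disputes no figure in the plan. The sample size is the figure that a loss of contrast would affect. Inputs from the Sample size section: difference δ = 0.1 m/s, SD σ = 0.3 m/s, two-sided alpha 0.05, power 80%, 140 per group.

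- Plan's figure: n per group = 2(1.96 + 0.842)² σ²/δ² = 2 × 7.85 × 0.09/0.01 ≈ 141.3, rounded up to 142, so 284 in total. The stated 280 is reproduced closely.
- Power at 140 per group: Φ(δ/(σ√(2/n)) − 1.96) = Φ(0.1/0.03586 − 1.96) = Φ(0.829) = 79.6%.

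If control-arm use of the fallback shrank δ by an **assumed** share:

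| Assumed loss of contrast | δ (m/s) | Power at 140 per group |
|---|---|---|
| 0% | 0.100 | 79.6% |
| 5% | 0.095 | 75.5% |
| 10% | 0.090 | 70.9% |
| 20% | 0.080 | 60.7% |

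Nothing in the article says which row applies, or that the contrast shrinks at all. If the calculation is done seated, the control arm loses gait practice, which could move the contrast the other way. The table shows only that the planned power has no slack.

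**The case against.** The strongest reply is that this is a drafting slip. Section {11b} starts with Table 1's sentence, appends Table 2's fallback and never states a DT rule, which looks like two rules merged when the article was condensed. The same section closes by saying that allocated interventions are not to be changed. The section on access to the full protocol identifies it with Tables 1, 2 and 3, and centres work from training visits and a study manual that is not shown. Nothing proves that any centre works from this paragraph. A slip is the likely explanation, and Table 1 is the better guide to intent. But the published text names the control arm and states a rule for it that conflicts with Table 1, so it still needs correcting.

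Second, the DT label is applied within the DT arm, where the exercises are done while walking; {11b} does not say that the ST patient walks while calculating. This stands as a limit on the claim: dual-task contamination is possible, not shown. It does not remove the conflict. Walking with calculation is dual-task training, and calculation without walking replaces a gait slot with a cognitive task. Neither fits a gait-only control.

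Third, use may be uncommon. Repetition is listed first, eligibility requires walking 10 m, and the lowest ST level is comfortable walking, so most patients should have something to repeat. That is a fair inference, and it is why no size of bias is claimed here.

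Fourth, section {11c} mentions that the protocol provides alternative exercises. For the ST arm, Table 1 provides none beyond repetition, so this does not reconcile the texts.

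**Conclusion.** The point holds as an internal contradiction about the content of the control arm. Section {11b} allows ST patients a calculation and counting fallback that Table 1 does not contain and that Table 2 reserves for the DT arm. Confidence in the mismatch is high, since it rests on a direct comparison of the texts.

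The consequence is not quantified. Each use would take 5 minutes, 20% of one session's exercise time or 1.7% of the programme's. Frequency of use, walking status, and the extent and direction of any bias cannot be obtained from the article. The point affects neither the estimand nor the planned analysis. It should be corrected because it concerns the contrast that the trial is designed to test.

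**What to change.** - Rewrite the sentence in {11b} so that the only ST fallback is repetition of the last gait exercise or session completed, as in Table 1.
- State in {11b} that the calculation and counting fallback belongs to the DT arm, as in Table 2.
- Send centres a short note confirming the rule.
- Where fallback use was recorded, report it descriptively by arm, so that readers can judge how far the control departed from gait exercise alone.
- Leave the primary intention-to-treat comparison as planned.

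The cost is one sentence, one note and, where the data exist, one descriptive table. Inclusion began in 2017 and recruitment was expected to finish in 2023, so the note helps only patients still to be treated. For the others, the gain is a clear definition of the control when the results are interpreted.
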